#### Secondary analysis

A similar procedure will be followed for secondary binary outcomes. We will use Cox proportional hazards regression to analyse survival outcomes. For continuous secondary outcomes we will use a two-sample *t*-test, transforming data where they are skewed.

### Exploratory moderator analysis

Additionally, for all primary and secondary analyses, we will carry out multivariable analyses, using generalised linear models, to adjust for the effects of stratification factors (for example, the previous immunosuppression regime). In this case, we will use the corresponding odds ratio to evaluate the adjusted size of the differences between proportions, by transforming back the estimated odds ratio associated with the treatment group into absolute differences in proportions. If the results of the analysis of the primary outcome are significantly affected, the adjusted effects will be taken as final.

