We hypothesise that the experimental treatment will bring the failure rate of group B2 down to that of biomarker negative patients in standard care (C). Assuming a 16% failure rate for group A2 (as in
[8]), and a 6% failure rate for group B2, 146 patients per group will provide 80% power and 5% type I errors, for a two-sided test.

The numbers enrolled in groups A and B include those patients initially enrolled in groups C or D who become HLA Ab + during re-screening.

We calculated the sample size needed to show the non-inferiority of all unblinded patients compared to all blinded patients as follows.

Hypothesis 2: All patients randomised to unblinded screening (combined groups B1 + B2 + D) will show equal or lower graft failure rates than all patients randomised to blinded screening (combined groups A1 + A2 + C), irrespective of biomarker status.

At the end of the trial, we expect 60% of patients to be in the HLA Ab– groups, 13% in DSA + groups and 27% in non-DSA + groups (after dropouts). Assuming a 6% failure rate in biomarker negative groups C and D, the estimated average failure rate of all blinded screening patients is 11.8% (that is, (6 × 0.6) + (16 × 0.27) + (30 × 0.13)). Similarly, the estimated average failure rate in the unblinded screening group is 7.3%. We have established a non-inferiority limit of 5% absolute difference, so that the unblinded group would be considered non-inferior with a failure rate of 16.8% or lower. For this purpose, 1,043 patients in each arm would provide 90% power and 2.5% (one-sided) type I errors.

We will keep recruiting until every group has acquired the number required to test both hypotheses. When calculating the number of patients to screen for eligibility and to recruit, the following assumptions were made: (1) 60% of patients under follow-up at each transplant centre will meet the eligibility criteria, (2) 10% will refuse consent, (3) the prevalence of HLA Ab in most transplant populations is 25% to 30%, (4) 6% of initially Ab– patients will become Ab + in each screening round and (5) 2% will drop out every screening round.

Based on these assumptions and a recruitment audit in participating centres, we have estimated that we need to assess eligibility for 4,672 patients and enrol 2,522 to ensure sufficient numbers are in each group at the primary end point to test both hypotheses. Figure 

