### Statistical analysis

#### Primary analysis

Statistical analysis will be on an intention-to-treat and treatment-received basis. We will consider the patients who become positive during the follow-up in the appropriate group.

The proportion of graft failures for each of the groups is denoted by π_A1_, π_B1_, etc.

Superiority (hypothesis 1):

H_0_: π_A1_ = π_B1_ and π_A2_ = π_B2_

H_1_: π_A1_ ≠ π_B1_ and π_A2_ ≠ π_B2_

To test superiority for the primary outcome for the biomarker (HLA Ab) positive groups (hypotheses 1.1 and 1.2), we will use a two-sided *Z*-test at the 5% level of significance, and will calculate the 95% CI for the difference in the proportion of graft failures between the biomarker-led care and standard care groups. The biomarker-led care groups will be considered superior if the absolute *Z* > 1.96, and our assumptions with respect to the size of the differences will supported if the CI includes a positive difference in proportions of 14% for hypothesis 1.1, and 10% for hypothesis 1.2.

Non-inferiority (hypothesis 2):

H_0_: π_Unblind_ – π_Blind_ ≥ δ

H_1_: π_Unblind_ – π_Blind_ < δ

To test for non-inferiority of the unblinded groups compared to the blinded groups (hypothesis 2), we will carry out a one-sided *Z*-test at the 2.5% level of significance. We will conclude non-inferiority if H_0_ is rejected, and the corresponding upper bound of the 95% CI excludes the limit δ (set at 5% more failures in the unblinded groups).

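### The adjusted analysis back-transforms one conditional odds ratio, which does not determine the population risk difference that the 5-point non-inferiority margin bounds

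*Protocol article*

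**What the plan says.** Hypothesis 2 compares all unblinded with all blinded patients on the difference in failure proportions. *Sample size calculations* sets the margin: "We have established a non-inferiority limit of 5% absolute difference". *Primary analysis* gives the decision rule: "we will carry out a one-sided *Z*-test at the 2.5% level of significance", with non-inferiority concluded if "the corresponding upper bound of the 95% CI excludes the limit δ (set at 5% more failures in the unblinded groups". The quantity bounded is therefore π_Unblind – π_Blind over the whole trial population.

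*Exploratory moderator analysis* then plans generalised linear models adjusted for the stratification factors, for all primary and secondary analyses. It expresses the adjusted effect "by transforming back the estimated odds ratio associated with the treatment group into absolute differences in proportions". If the primary-outcome results change significantly, "the adjusted effects will be taken as final".

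*Trial design* lists the stratification factors: antibody status (DSA+, non-DSA+, HLA Ab–), current immunosuppression and site. The expected mix is stated as "we expect 60% of patients to be in the HLA Ab– groups, 13% in DSA + groups and 27% in non-DSA + groups (after dropouts".

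**The concern.** The treatment odds ratio from such a model is conditional on antibody stratum, and the planned risks differ five-fold between strata. The same odds ratio then means a different absolute difference in each stratum. Applying it to the overall rate does not give the population difference either, because odds ratios are not collapsible: the conditional odds ratio is further from 1 than the one that links the two overall rates.

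At stake is the adjusted check against the 5-point margin. If the converted figure is systematically larger than the population difference near the margin, the check no longer has its nominal 2.5% error and loses power. If the base rate for the conversion is left open, so is the quantity being compared with δ.

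**Working it through.** **Inputs (*Sample size calculations*).** Shares 60/27/13% for HLA Ab–, non-DSA+ and DSA+. Standard-care failure rates 6/16/30%. Margin 5 points, 1,043 per arm, one-sided 2.5%.

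**The plan's own figures.**
- Blinded rate: 0.60×6 + 0.27×16 + 0.13×30 = 11.82%, matching the stated 11.8%.
- Unblinded rate: 0.60×6 + 0.27×6 + 0.13×16 = 7.30%, as stated.
- Sample size: 11.8% against 16.8% at 90% power needs 1,029 per arm (pooled variance), 1,025 (unpooled) or 1,023 (arcsine), all within 2% of 1,043. With equal true rates of 11.8% the usual non-inferiority formula needs 875, and 1,043 gives 94.3% power.

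**Conversion formula.** For base risk p0 with odds o = p0/(1 – p0), an odds ratio OR gives p1 = OR·o/(1 + OR·o), and the difference is p1 – p0.

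**Harm exactly at the margin, common odds ratio.** Solving for the OR whose share-weighted difference is 5 points gives 1.559:

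| Base rate | o | OR·o | p1 | Difference (points) |
|---|---|---|---|---|
| 6% | 0.0638 | 0.0995 | 9.05% | 3.05 |
| 16% | 0.1905 | 0.2970 | 22.90% | 6.90 |
| 30% | 0.4286 | 0.6682 | 40.05% | 10.05 |
| Overall 11.82% | 0.1340 | 0.2090 | 17.29% | 5.47 |

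Check: 0.60×3.05 + 0.27×6.90 + 0.13×10.05 = 5.00. Conversion at the overall rate overstates the population difference by 0.47 points.

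**Where the decision differs.** The odds ratio linking 16.8% and 11.8% is (0.168/0.832)/(0.118/0.882) = 1.509. An upper confidence limit between about 1.51 and 1.56 therefore fails when converted at the overall rate and passes when averaged over patients. At 1.55 the two figures are 5.38 and 4.92 points.

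**Error at the margin.** Trials were simulated with 1,043 per arm and the margin-sized harm above. The logistic model contained arm and antibody stratum. For the conversions, the upper 95% limit of the odds ratio was converted and compared with 5 points. In 20,000 trials non-inferiority was declared in:
- 0.7% when converting at the observed overall blinded rate (other, smaller runs gave 0.4–0.7%);
- 1.4% when converting the same upper limit within each stratum and averaging over patients;
- 2.6% with the standardised risk difference and a delta-method interval;
- 2.5% with the planned unadjusted comparison.

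The conservatism thus has two sources: the base rate, and converting a confidence limit instead of building an interval for the difference.

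**Power.** With equal true rates in every stratum, the same simulation declares non-inferiority in 87% of trials (overall-rate conversion), 96% (standardised) and 94% (unadjusted).

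**Under the planned benefit.** The planned stratum odds ratios are 1.00, 0.34 and 0.44. The fitted common odds ratio is about 0.576 (95% CI 0.42 to 0.78). At the overall rate this converts to –4.66 points against a true 7.30 – 11.82 = –4.52. The upper limit is below 1, so it converts to a negative difference at any base rate and non-inferiority is concluded in every case.

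**The case against.** The strongest reply has four parts.

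*It is detail for the analysis plan.* The article is condensed, and base rate, averaging and interval method may be fixed in a plan that is not shown. That stands for missing detail. It does not cover what the text commits to, which is converting the one treatment odds ratio. Averaging each patient's predicted risks under both arms is a different procedure, although nothing in the text forbids it.

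*The scale is right.* A reader might infer that the adjusted decision is made on the odds-ratio scale. It is not: the text returns to absolute differences, the scale of δ. The defect lies in which absolute difference results.

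*The alarming error rate is not the plan's.* A reader might also infer a badly inflated error. Reading the population difference off the antibody-negative stratum alone would pass margin-sized harm in roughly 35% of trials. No section proposes that base rate, and it would contradict the all-patient contrast in *Primary analysis*. The figure should not be charged to the plan.

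*The adjusted result may not decide hypothesis 2.* The section is headed exploratory, and its override names the primary outcome. *Primary end points* limits that to HLA Ab+ patients, and *Secondary end points* lists the all-patient failure rate. But hypothesis 2 is tested under *Primary analysis*, so the reach of the override is unclear. An adjusted hypothesis 2 estimate is produced either way.

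It is also fair that a common harm of odds ratio 1.56 is artificial: antibody-negative patients keep their existing therapy in both arms and are assumed to fail at 6% in both. Error control at the margin still needs some scenario there, and the size quoted belongs to this one.

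**Conclusion.** The point holds in limited form. The planned back-transformation yields an absolute difference, but not one that is determined as, or in general equal to, the population difference bounded by the 5-point margin. With the natural choice of the overall rate, it overstates a true 5-point harm by about half a point and cuts the one-sided error from 2.5% to about 0.4–0.7%. The cost is power: about 87% instead of 96% if the arms are truly equal.

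These sizes assume the planned stratum mix and rates, a common odds ratio, adjustment for antibody stratum only, and conversion of the upper confidence limit. The article states neither the base rate nor the interval method.

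Two consequences should not be inferred. The expected non-inferiority conclusion would not change under the planned benefit. The superiority tests of hypotheses 1.1 and 1.2 against zero cannot flip through the choice of base rate, since each is made within one antibody stratum and an odds ratio of 1 converts to zero at any base rate.

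**What to change.** In *Exploratory moderator analysis*, replace the odds-ratio back-transformation with the standardised risk difference:

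1. Fit the same logistic model with arm and the stratification factors.
2. Predict each patient's risk under both arms.
3. Average each set of predictions over all patients in the comparison and take the difference.
4. Give it a delta-method or bootstrap 95% CI.
5. For hypothesis 2, compare the upper bound with δ.

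State in the same section whether this adjusted result can override the hypothesis 2 Z-test or only supports it.

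The cost is a change of wording and a few lines of code, with the same model, data and patients.

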### Sample size calculations

The primary purpose of this trial is to demonstrate superior outcomes using a defined treatment strategy compared to standard care for biomarker (HLA Ab) positive patients. Once superiority is demonstrated for HLA Ab + patients, it is also necessary to demonstrate non-inferior outcomes when comparing the unblinded screening strategy to the blinded standard of care for the entire patient population, including those HLA Ab–. The graft failure rate 3 years after screening has been chosen as a clinically relevant primary outcome. As a reference for power calculations, we have used the observed failure rates reported by Lachmann *et al*.
[8] for HLA Ab + and HLA Ab– patients. Since failure rates differ between DSA + and non-DSA + patients, sample size calculations have been carried out separately for these groups. Following these calculations, we estimated the number to be screened, based on expected dropout rates, expected screening results and eligibility criteria (see below). We based our estimates of the differences in primary outcome between the groups on, first, the results of our preliminary data from patients with CR treated with a similar regime as used here, and second, our assessment that large differences in primary outcome will be needed to make the screening programme cost-effective.

Hypothesis testing will be sequential
[11]. Superiority will be tested first in the HLA Ab + groups to demonstrate the efficacy of the treatment. If this analysis is significant, then non-inferiority will be tested for the entire population to demonstrate the clinical utility of the biomarker screening. We calculated the sample size needed to show the superiority of the treatment optimisation for biomarker-positive patients using the hypotheses as follows.

Hypothesis 1.1: HLA Ab + patients with DSA, randomised to standard care (A1) will show higher graft failure rates than patients randomised to biomarker-led care (B1).

We hypothesise that the experimental treatment will bring the failure rate of group B1 down to that of non-DSA patients in standard care (A2). Assuming a 30% failure rate for group A1 (as in
[8]), and a 16% failure rate for group B1, 139 patients per group will provide 80% power and 5% type I errors, for a two-sided test.

Hypothesis 1.2: HLA Ab + patients, with non-DSA, randomised to standard care (A2) will show higher graft failure rate than patients randomised to biomarker-led care (B2).

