### Randomisation procedure and code break

Prior to randomisation but after consent, site staff will register a recruit on the web-based electronic data capture system (InferMed MACRO), hosted at the King’s Clinical Trials Unit (KCTU). Each will be assigned a unique study patient identification number (PIN) by the system. Samples from all recruits will be sent to the HLA laboratory, along with this PIN and a sample request form containing other information required for randomisation.

Laboratory staff will screen for HLA Ab and perform SAB testing on positive screening samples to check for the presence of DSA. Once this information is known, the lab staff will access the KCTU randomisation system and randomise the patient, using the HLA Ab results. Randomisation will be further stratified by centre and current immunosuppression. The lab staff, PIs and nurses at the site will be automatically emailed and the randomisation system will inform them whether the patient is in a blinded or unblinded group. If the patient is in an unblinded group, the system will inform the PI of the HLA Ab status. Unblinded patients will be identified by blue stickers appended to the notes and all future clinical samples. The system will tell the trial staff to enter HLA Ab– patients into the subsequent 8-monthly screening rounds, and also whether the patients have been selected to provide future samples for the 4-monthly scientific analysis (for transfer to the chief investigator’s laboratory). This information will be relayed using a star on the blue labels that are appended to the laboratory request forms.

The notes and samples from blinded patients will have green stickers and labels. The HLA Ab status will not be given to the PIs or trial staff. A star will be used to tell the trial staff which recruits have been selected to provide 4-monthly samples for transfer back to the chief investigator’s lab for scientific analysis. These patients will have samples taken every 8 months for HLA Ab screening. Once inside the lab, the lab staff will use their knowledge of the HLA status to determine which HLA Ab– patients will undergo screening. The samples from HLA Ab + patients will be discarded.

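### The protocol lets an exploratory adjusted model replace the primary Z-test on an undefined, result-dependent trigger, so no single primary test, estimate and interval is fixed

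*Protocol article*

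**What the plan says.** Under Primary analysis, for hypotheses 1.1 (DSA+) and 1.2 (non-DSA+): "we will use a two-sided *Z*-test at the 5% level of significance". The decision rule is "The biomarker-led care groups will be considered superior if the absolute *Z* > 1.96", accompanied by a 95% CI for the difference in proportions. The same section opens with "Statistical analysis will be on an intention-to-treat and treatment-received basis" and does not rank the two.

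Under Exploratory moderator analysis, generalised linear models adjusted for the stratification factors are added for all primary and secondary analyses. The adjusted effect is obtained "by transforming back the estimated odds ratio associated with the treatment group into absolute differences in proportions". The section ends: "If the results of the analysis of the primary outcome are significantly affected, the adjusted effects will be taken as final".

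Two other passages bear on this:

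- Sample size calculations makes testing sequential. Non-inferiority in the whole population is tested only if the superiority analysis is significant.
- The randomisation section states, beyond antibody status, "Randomisation will be further stratified by centre and current immunosuppression". Trial design gives four immunosuppression groups and five sites.

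**The concern.** An analysis labelled exploratory can overrule the confirmatory one, and whether it does so depends on how the two results compare. The trigger could mean a flipped conclusion, a changed p-value or a shift in effect size. These readings lead to different final results from the same data.

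Three things depend on the choice: the verdict on superiority, the estimate and interval that are reported, and the opening of the non-inferiority test. A trial whose primary result can be selected after both candidates are known cannot guarantee its stated 5% level. A later reader also could not tell from the protocol which result was meant to count.

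**Working it through.** **1. The protocol's own figures.** Sample size calculations gives hypothesis 1.1 as 30% v 16% with 139 per group, and hypothesis 1.2 as 16% v 6% with 146 per group. Both are at 80% power and 5% two-sided. The arcsine formula reproduces them:

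n = 2(z₀.₉₇₅ + z₀.₈₀)² / h², with h = 2(arcsin√p₁ − arcsin√p₂)

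- 1.1: h = 0.3362, n = 138.8, rounded up to 139
- 1.2: h = 0.3281, n = 145.8, rounded up to 146

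The threshold |Z| > 1.96 corresponds to a two-sided 5.0%. The planned level and sizes therefore belong to one unadjusted test.

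**2. Reading A: the trigger is a changed conclusion.** The four cases are:

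| Unadjusted | Adjusted | Final decision |
|---|---|---|
| significant | significant | significant |
| not | not | not |
| significant | not | adjusted taken: not |
| not | significant | adjusted taken: significant |

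The last column always equals the adjusted column, so the |Z| > 1.96 rule never decides anything. The reported estimate and CI still come from one analysis in some outcomes and from the other in the rest.

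**3. Reading B: the trigger is a shift in the estimate, or discretion.** This was simulated under the null with 10,000 trials per scenario (Monte Carlo standard error √(0.05 × 0.95/10,000) ≈ 0.2 points). Both hypotheses were covered: 139 per group at 30% and 146 per group at 16%. The unadjusted Z-test was compared with a logistic model containing four immunosuppression groups and five sites.

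Three inputs are assumptions, because the documents do not give them: the prognostic strength of the strata (three levels, none to strong), a 10% change in log odds ratio as a trigger, and 30% later converters not balanced by stratum. Ranges are over both hypotheses and all three strengths.

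| Type I error, % | Full stratified balance | 30% converters unbalanced | No stratified balance |
|---|---|---|---|
| Unadjusted only | 2.9–5.2 | 3.4–5.0 | 4.7–5.6 |
| Adjusted only (= reading A) | 5.0–5.5 | 4.9–5.4 | 5.1–5.5 |
| Switch if log OR moves >10% | 5.0–5.4 | 5.2–5.8 | 5.6–6.3 |
| Worst case: either test accepted | 5.1–5.5 | 5.4–5.9 | 6.2–7.5 |
| Tests disagree | 0.3–2.5 | 0.8–2.7 | 1.5–4.4 |

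The low values in the first row come from stratified randomisation on prognostic factors that the analysis then ignores. The standard error is too wide and the test becomes conservative.

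**4. Scale of the adjusted estimate.** One odds ratio does not give one absolute difference. For hypothesis 1.1, OR = (0.16/0.84)/(0.30/0.70) = 0.44. Applied to a control risk of 30% it gives 16.0%, a difference of 14.0 points. At 20% it gives 10.0%, a difference of 10.0 points. At 16% it gives 7.8%, a difference of 8.2 points. The protocol compares its intervals with absolute targets (14% and 10%) and an absolute 5% margin, so the standardisation should be named together with the primary analysis.

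**The case against.** The strongest reply is that the freedom is narrow. The covariates are the stratification factors, named in advance, so there is no searching among adjustments. The rule also runs one way only, towards the adjusted model, including when adjustment removes significance. On the most natural reading (reading A) the level is close to 5%. All of this stands, and it limits the size of the problem.

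A reader might infer that the true error rate is 6–7%, from the chance that at least one of two correlated Z statistics exceeds 1.96 (6.1% at correlation 0.97, 6.5% at 0.95, 7.0% at 0.90). The arithmetic is right, but the documents do not support that conclusion. The text does not say that either test may win. The correlations are assumed, and at 0.99 the result is 5.7%. The calculation also treats the unadjusted Z as standard normal, whereas stratified randomisation on prognostic factors makes it conservative.

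Two further inferences should be held back. Antibody status is already respected for superiority, because DSA+ and non-DSA+ patients are tested separately. The unranked pair of intention-to-treat and treatment-received analyses and the back-transformation method are secondary: a separate analysis plan, not shown, may settle them.

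That plan might also define the trigger. But the objection is to a rule that the protocol states. Defining the trigger would still leave the final result chosen by the data, unless the rule itself were withdrawn.

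**Conclusion.** The point holds as a defect of specification. The two analysis sections together do not fix one primary test, estimate and interval, and the undefined choice carries through to the gate for hypothesis 2.

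The effect on type I error is small under the stated design. It is near 5% if the trigger is a changed conclusion, and about 5.1–5.9% in the worst case with stratified randomisation, including the scenario with unbalanced converters. The 6.2–7.5% range is an upper scenario that needs the stratified balance to be absent, which the protocol's randomisation contradicts. These figures rest on the assumed prognostic strengths and share of converters. If the factors are prognostic, the unadjusted test named as primary errs the other way, down to 2.9% in simulation. That is a further reason to settle on the adjusted analysis from the start.

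**What to change.** Delete the sentence that makes the adjusted effects final. Name one primary analysis before outcome data are seen:

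- Intention-to-treat set.
- Hypotheses 1.1 and 1.2: separate models in DSA+ and non-DSA+ patients, adjusted for immunosuppression group and site.
- Hypothesis 2: the same factors plus antibody status.
- Effect measure: standardised (marginal) risk difference with a 95% CI by the delta method or bootstrap, so that it is on the same absolute scale as the 5% margin. The superiority decision and the gate to hypothesis 2 are both taken from this analysis.
- The unadjusted Z-test and the treatment-received analysis are labelled supportive.

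Cost: a wording change and slightly more analysis work. The factors are already collected for randomisation, and 139 and 146 per group stand.

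The main downside is sparse strata. At the planned rates hypothesis 1.2 expects 146 × (0.16 + 0.06) ≈ 32 failures, against (4 − 1) + (5 − 1) = 7 covariate terms plus treatment. A rule for merging sites or immunosuppression groups with few events should therefore be written in advance, without reference to results by arm.
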